## Abstract

**Introduction:**

Pulmonary segmentectomy, when combined with hilar and mediastinal lymphadenectomy, is currently considered the gold standard treatment for early-stage lung tumors (NSCLC) smaller than 2 cm in diameter. The preoperative planning for segmentectomies usually includes a contrast-enhanced CT with 2D reconstructions (axial, coronary, and sagittal). Recent technological advances allow 3D (volume rendering) reconstructions of preoperative CT scans, intended to improve the surgeon’s understanding of the segmental anatomy.

The study aims to investigate the added value of 3D reconstruction in enhancing the surgeon’s understanding of anatomical structures, thus facilitating surgical planning and improving oncological outcomes.

**Methods and analysis:**

This is a prospective, randomized, controlled study.

Patients will be randomized into two groups:

1. Group 2D: the preoperative workup for these patients will consist of a contrast-enhanced chest CT with two-dimensional (2D) reconstructions (axial, coronary, and sagittal);

2. Group 3D: the preoperative workup for these patients will consist of a contrast-enhanced chest CT with two-dimensional (2D) reconstructions (axial, coronary, and sagittal) and a 3D reconstruction (volume rendering) of the same chest CT employing dedicated software.

The primary endpoints will be negative margin (R0) resection rate, resection margin (staple line-to-tumor distance), and thoracotomy conversions.

We will use Fisher’s exact test for binary outcomes and Mann–Whitney *U* test for continuous outcomes. For subgroup analyses, we will use regression. Multivariable analyses will be based on logistic regression for binary outcomes and linear regression for continuous outcomes.

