### Primary objective

The primary objective is to determine if 2D + 3D reconstruction compared to 2D improves the oncological radicality of sublobar resections and prevents major intraoperative complications.

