### Outcomes (see supplementary file for outcome definition)

Primary outcomes measuresDisease-free resection margin. This measure of success was selected because it was considered clinically and oncologically relevant after segmentectomy and represented a prerequisite and necessary quality control. A disease-free resection margin > 2 cm is mandatory, and a significant result could improve clinical practice and therapeutic outcomes.Evaluation of conversions from minimally invasive to thoracotomy procedure. It is still unclear whether preoperative 3D anatomical reconstruction can reduce the incidence of major intraoperative events, which usually require a traditional thoracotomy. This measure of success, if significant, will increase patient safety.

Secondary outcomes measuresEvaluation of operating timesEvaluation of intraoperative blood lossEvaluation of vascular lesionsEvaluation of intraoperative air leaks and the use of sealantsEvaluation of postoperative air leaksEvaluation of postoperative hospitalization length

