### Sample size

No data in the current literature was found about the other primary outcome margin- and disease-free resection. Therefore, the sample size was calculated based on the primary outcome conversions from minimally invasive to thoracotomy procedure.

To calculate sample size, we use data about conversion derived from previous literature [17–21]. The conversion rate for patients in the 2D group is estimated to be 9.4% [19]; the retrospective study has shown a reduction to 2.6%. Therefore, the required sample size to confirm superiority was 274, with a power of 80%, a one-sided significance level of 0.05, an accrual period of 3 years, and a follow-up period of 1 month. The planned total sample size was set at 288 patients to account for loss at follow-up.

Systematic methods such as reminders to contact patients, make appointments, and monitor retention will be employed to improve participant retention and will not expenses for follow-up visits and procedures.

We have used for the sample size determination the R software (package pwr) [26].

Two pre-specified interim analyses were conducted after the accrual of half of the planned patients and after accrual completion. To keep the study at a 5% one-sided significance level, we used the Lan–DeMets alpha-spending function [27] with an O’Brien–Fleming approach [28].

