### Statistical methods

We do not expect a relevant degree of missing data. Methods of multiple imputations (bagged trees imputation) will be used to calculate missing values.

Multivariable analyses will be based on logistic regression for binary outcomes and linear regression for continuous outcomes.

We will examine the residual to assess model assumptions and goodness-of-fit. *P*-values will be reported to three decimal places, with *p*-values less than 0.001 reported as *p* < 0.001. All analyses were performed using the R Statistical Software (4.2.2; R Core Team 2022). We will use 2-sided *p*-values with alpha ≤ 0.05 significance level for all tests.

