### Harms

An adverse event is not really expected in our study for the type of study we conduct. The primary outcomes are disease-free surgical margins and thoracotomy conversions, which we will collect to verify any differences between the two groups. Adverse events, if any, will be collected after the subject has provided consent and enrolled in the study.

Unexpected harms will be collected systematically through a specific request to each participant at each follow-up visit. Harms will be collected and analyzed using standard grading criteria according to the Common Terminology Criteria for Adverse Events (CTCAE) [31].

Any adverse event that occurs between study enrollment and hospital discharge will be reported to the local IRB (institutional review board).

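### The primary endpoints number three in the abstract and two elsewhere, and no success rule or alpha allocation secures the 5% study level that the protocol aims for

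*Protocol article*

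**What the plan says.** **Which endpoints are primary.** The abstract (Methods and analysis) lists three: "The primary endpoints will be negative margin (R0) resection rate, resection margin (staple line-to-tumor distance), and thoracotomy conversions". The Outcomes section lists two, a disease-free resection margin and "Evaluation of conversions from minimally invasive to thoracotomy procedure". The Harms section agrees with two: "The primary outcomes are disease-free surgical margins and thoracotomy conversions". The Sample size section likewise treats margin as the one other primary outcome.

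**What counts as success.** The Outcomes section presents each outcome as a success measure in its own right. Of the margin it says "A disease-free resection margin > 2 cm is mandatory, and a significant result could improve clinical practice and therapeutic outcomes"; of conversion, "This measure of success, if significant, will increase patient safety". The Primary objective asks whether adding 3D reconstruction "improves the oncological radicality of sublobar resections and prevents major intraoperative complications". No section says whether one significant outcome is enough or both are needed.

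**Which alpha applies.** The Statistical methods section prescribes two-sided p-"values with alpha ≤ 0.05 significance level for all tests". The Sample size section uses one-sided 0.05 and describes alpha spending to hold the study at 5% one-sided. That spending covers repeated looks, not several endpoints. On sizing, "the sample size was calculated based on the primary outcome conversions from minimally invasive to thoracotomy procedure".

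**The concern.** The protocol aims at a 5% study level but gives two or three primary tests 0.05 each, with nothing to tie them together. If any one of them can carry the superiority claim, the level for that claim exceeds the level of a single test. If all must be met, the level is safe, but the power calculation, made for conversion alone, no longer describes the trial's chance of success. The text leaves both readings open, so neither the error rate nor the power of the confirmatory claim is fixed. The conflict between one-sided and two-sided 0.05 changes the error figures by a factor of about two.

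**Working it through.** **1. The plan's own sample size.** Inputs from the Sample size section: conversion 9.4% vs 2.6%, power 80%, one-sided 0.05, R package pwr (arcsine effect size). Allocation is 1:1 (Trial design).
- h = 2·asin(√0.094) − 2·asin(√0.026) = 0.2993
- n per arm = 2·((1.645 + 0.842)/0.2993)² = 138.0, so 276 to 278 in total, against the stated 274. Power at 137 per arm is 79.7%.

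The figure is reproduced closely with a single test at the full one-sided 0.05. No alpha is set aside for another endpoint.

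**2. Nominal false superiority rate if any one endpoint suffices** (independent tests, no true effect), 1 − (1 − a)^k:

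| Rule | a per test in favour of 3D | k = 1 | k = 2 | k = 3 |
|---|---|---|---|---|
| One-sided 0.05 (Sample size) | 0.05 | 5% | 1 − 0.95² = 9.75% | 1 − 0.95³ = 14.26% |
| Two-sided 0.05 (Statistical methods) | 0.025 | 2.5% | 1 − 0.975² = 4.9% | 1 − 0.975³ = 7.3% |

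**3. Correlation.** R0 status and margin distance come from the same specimen, so positive correlation is likely (an assumption). Simulated normal tests with a common correlation, one-sided 0.05: at 0.5, 8.7% (two) and 11.7% (three); at 0.9, 6.7% and 7.9%. Independence is therefore the upper case as long as correlation is not negative.

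**4. Fisher's test.** The abstract assigns Fisher's exact test to binary outcomes. Its exact size was enumerated at 144 per arm (288/2), one-sided 0.05:
- Conversion: 2.8% at a common rate of 6% (the mean of 9.4% and 2.6%) and 3.25% at 9.4%.
- R0 failure: 1.4% at a rate of 2% and 2.6% at 5%. These rates are assumed; the document gives none.
- Margin distance (Mann–Whitney): taken as 5%.

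Combined under independence:

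| Primary set | One-sided 0.05 | Two-sided 0.05, claims for 3D only |
|---|---|---|
| Conversion, R0, distance | 8.9–10.5% | 4.3–5.2% |
| Conversion, distance | 7.7–8.1% | 3.8–4.0% |
| Conversion, binary R0 | 4.2–5.8% | 1.8–2.7% |

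Check of the highest value: 1 − (1 − 0.0325)(1 − 0.0262)(1 − 0.05) = 10.5%.

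**5. If all must be met.** The false-positive rate is at most 5%. Power falls: Fisher's test for conversion has 72.6% power at 144 per arm, one-sided 0.05. With an assumed 80% for margin and independence, joint power is 0.726 × 0.80 = 58%.

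**6. If alpha were split.** A Bonferroni split of one-sided 0.05 would need, by the arcsine formula, about 352 evaluable patients for conversion (two endpoints) or 394 (three). At 274, its power falls from 79.7% to 69.8% or 63.7%.

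**The case against.** The strongest reply is that the document nowhere says that one significant endpoint is enough. A reader might infer this from the way the Outcomes section treats each outcome as its own success measure, but the Primary objective joins the two aims with *and*. On a both-required reading there is no inflation. This stands: the any-one rule is a possible reading, not the plan's stated rule. It does not remove the point, because no section states the both-required rule either, and the sample size does not allow for it.

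A reader might also take 10–14% as the trial's actual false-positive rate. The document does not support that. Those values need one-sided 0.05, independence and tests that use their full size. Under the two-sided rule the nominal values are 4.9% and 7.3%, and the two-endpoint value is then numerically within a 5% one-sided level. With conversion plus a binary margin and Fisher's test, the rate is close to what a single test allows. This also stands, and it limits the size of the point.

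Finally, one might argue that the margin > 2 cm is a further primary test, or that the choice among margin versions stays open until the data are seen. Neither is established. The Outcomes section presents > 2 cm as a requirement, not as a separate hypothesis, and refers to a supplementary file for outcome definitions that is not at hand. That file may define the margin outcome. It would not reconcile the printed lists of three and two, nor replace the printed instruction to use 0.05 for every test.

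**Conclusion.** The point holds as a defect of specification. The primary list is inconsistent within the article, sidedness is contradictory, and no rule links the primary tests to the 5% one-sided level that the study is meant to keep. If any one endpoint suffices, the nominal false superiority rate could reach about 10% (two endpoints) or 14% (three) at one-sided 0.05, or 4.9% and 7.3% at two-sided 0.05 against 2.5% for a single test.

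Allowing for Fisher's conservatism at one-sided 0.05, about 9–10% is more realistic for three endpoints and about 8% for conversion plus a continuous margin. This rests on independence, on 144 per arm and, for three endpoints, on an assumed 2–5% R0 failure rate. Positive correlation lowers it further. If all endpoints must be met, error is at most 5% and the cost is power. Because the confirmatory claim depends on which reading applies, the rule should be fixed before outcome data are seen.

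**What to change.** 1. Give one list of primary endpoints, worded identically in the abstract, Outcomes and Harms sections.
2. State one sidedness for the Sample size and Statistical methods sections. If two-sided 0.05 is kept, the arcsine formula gives about 352 evaluable patients rather than 274 for 80% power on conversion.
3. Replace the blanket 0.05 for every test with a stated success rule that controls the familywise error. One sound choice is a fixed sequence: test conversion, the powered endpoint, first at the full alpha; test one defined margin endpoint at the same alpha only if conversion is significant; make the other margin versions secondary. A both-required rule or an alpha split would also settle the matter, but each costs power, as shown above.

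The fixed sequence costs protocol and registry wording only. At a given sidedness, power for conversion is unchanged. Its downside is that margin cannot be claimed as confirmatory if conversion fails. The sponsor should weigh this, because the Primary objective names oncological radicality first.

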**Ethics and dissemination:**

The protocol and the model informed consent forms have been reviewed and approved by the ethics committee (N.: 1–2023) concerning scientific content and compliance with applicable research and human subject regulations.

A Subcommittee on Publications was established to review all publications and report its recommendations to the steering committee. The anonymized participant-level dataset and statistical code for generating the results will not be publicly available.

**Trial registration:**

The protocol was registered at ClinicalTrials.gov (ID: NCT05716815; Prospective rAndomized sTudy efficaCy tHree-dimensional rEconstructions Segmentectomy - Full-Text View - ClinicalTrials.gov). Jan 19, 2023.

**Supplementary Information:**

The online version contains supplementary material available at 10.1186/s13063-023-07600-w.

## Introduction

### Background and rationale

#### Introduction

Lung cancer remains the leading cause of cancer mortality worldwide [1, 2]. Although lung cancer treatment today includes effective, innovative treatments, surgical resection is still the gold standard in the early stages [3, 4]. Minimally invasive thoracic surgery (MITS), such as video-assisted thoracoscopic surgery (VATS) and robotic thoracoscopic surgery (RATS), has achieved remarkable results in the treatment of early-stage non-small cell lung (NSCLC) [5–7] and is now preferred to traditional thoracotomic surgery. Segmentectomy for early-stage lung cancer has been shown to have an excellent long-term prognosis because it removes the neoplastic lesion and protects lung function [8, 9], and when combined with hilar and mediastinal lymphadenectomy, it can achieve a satisfactory oncological outcome [10, 11]. Recently, JCOG0802 confirmed that segmentectomy is the standard procedure for stage IA lung cancer (tumor diameter ≤ 2 cm; consolidation-to-tumor ratio > 0.5) [12].

Segmentectomy, defined in accordance with Oziumi H. et al. [13], requires the surgeon to know the location of the tumors to be removed, i.e., the anatomy of lobes, segments, bronchi, arteries, and veins to be resected. Sublobar resection is more technically demanding than a lobectomy because the anatomy of the pulmonary segments is more complex. Furthermore, vascular and bronchial variations of segments are common [14].

#### Mechanisms

Detailed preoperative planning and simulations of anatomical sub-lobar resection using 3D technology could contribute significantly to a safer operation. With the development of imaging technology, such as multidetector computed tomography (MDCT) and three-dimensional computed tomography bronchography and angiography (3D-CTBA), two-dimensional (2D) images can be converted into three-dimensional (3D) images [15, 16].

#### Existing knowledge

Recently, some retrospective studies [17–22] demonstrated that before performing minimally invasive (MI) lung segmentectomy, 3D reconstruction might guarantee margin- and disease-free resections, reduces thoracotomy conversions and intraoperative blood loss, shortens the operation time, and prevents postoperative air leakage, reducing hospitalization times and costs.

#### Need for a trial

3D reconstruction has long been widely used in vascular surgery departments to plan any endovascular repair procedure of the abdominal or thoracic aorta. A randomized trial is needed to demonstrate the utility and efficacy of using 3D reconstruction even before MI lung segmentectomy.

#### Rationale

Today, conventional computed tomography with 2D reconstruction is the gold standard method for planning MITS. With advances in imaging technology, a 3D reconstruction could improve surgeon practice, patient outcomes, and safety [23, 24].

#### Choice of comparator

The comparison group in our study is mandatory because it represents the current standard that all surgeons perform—patients with standard 2D CT reconstruction.

## Objectives

### Research hypothesis

3D reconstruction is superior to 2D for MI lung segmentectomy planning.

### Primary objective

The primary objective is to determine if 2D + 3D reconstruction compared to 2D improves the oncological radicality of sublobar resections and prevents major intraoperative complications.

### Secondary objectives

The secondary objective is to assess the efficacy of 2D + 3D reconstruction in reducing minor intraoperative complications.

### Trial design

The PATCHES trial is designed as a randomized, controlled, multicenter superiority trial with two parallel groups. Randomization will be performed as block randomization with a 1:1 allocation.

## Methods: participants, interventions, and outcomes

For the drafting of the article, we used the SPIRIT reporting guidelines (Figs. 1 and 2) [25].

**Fig. 1 Fig1:**

SPIRIT reporting checklist

**Fig. 2 Fig2:**
[figure not shown]
SPIRIT figure for the schedule of enrolment, interventions, and assessments

### Study setting

#### Country selection

Ten international high-volume thoracic surgery departments currently participate in the study design. We have included three continents: Europe (Italy, Germany, Belgium), Asia (Hong Kong and Palestine), and the USA (Boston, MA). We selected centers with significant cultural differences to demonstrate the reproducibility of the proposed intervention.

#### Definition of community

To achieve the required sample size with the desired power, the number of segmentectomies at the sites must be high enough. We chose the participating sites so that the average number of annual MI procedures across all communities in the study could reach at least 20 patients per site. Our final selection of sites combines university centers (Marburg, Germany; Salamanca, Spain; Belgrade, Serbia, Harvard Boston, USA; Leuven, Belgium; Hong Kong, China) and hospital centers (Bolzano, Italy, IEO Milan, Italy, Jerusalem, Palestine, Potsdam, Germany).

We e-mailed the trial protocol to recruit participating sites to an extensive list of MI thoracic surgery centers worldwide. The centers listed above have decided to join and have received the relevant material and the approval of the ethics committee of the coordinating center. After approval by each ethics committee, the site will begin enrolling patients.

### Eligibility criteria

Patients (or a representative) must provide written, informed consent before any study procedures occur.

Inclusion criteria

Patients eligible for the trial must comply with all the following at randomization:Segmentectomy performed through a MI approach (VATS or RATS)Pathologically proven NSCLC on the resected specimenAge ≥ 18

Exclusion criteriaPrior homolateral cardiothoracic surgeryAllergy or any other contraindication to iodinated contrast mediaSegmentectomy performed through an open approach (thoracotomy)Histology different than NSCLCPregnancy

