### Participant timeline

Patients with tumors < 2 cm in diameter and suspicion of malignancy will undergo CT and be discussed at the Multidisciplinary Board of Thoracic Oncology. Patients selected for MI segmentectomy will conduct an informational interview and possibly sign the consent to the study. Patients who agreed to participate will be randomized into two groups:Group 1: 2D + 3D reconstructionGroup 2: 2D reconstruction (control group)

Subsequently, a database will prospectively collect intraoperative and postoperative data. The follow-up will be closed one month after surgery (Fig. 3).

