### Data collection

The measures of outcomes will be collected by medical or nursing staff based on official patient records. Alerts will be sent via e-mail, marking the phases of entering the outcomes on the REDCap software concerning the intervention date. Any data upload delay of more than 2 months will be disclosed in the study. Primary outcomes are not allowed to be missing. The presence of the missing data will be communicated to both the coordinator of the participating center and the data managers. Reasons for missing data will be recorded.

Study data will be collected and managed using REDCap electronic data capture tools hosted at Regional Hospital, Bolzano, Italy [29, 30]. REDCap (Research Electronic Data Capture) is a secure, web-based software platform designed to support data capture for research studies, providing (1) an intuitive interface for validated data capture, (2) audit trails for tracking data manipulation and export procedures, (3) automated export procedures for seamless data downloads to standard statistical packages, and (4) procedures for data integration and interoperability with external sources.

Access to the study data will be restricted, and participating centers will only have access to their data. Incremental data back-ups will be performed daily.

Data collection takes place at regular intervals after surgery (1, 15, 30 days). Regular reminders will be sent to the coordinator of the participating center for operative and postoperative data to be entered in due course.

Participating centers are encouraged to enroll and randomize eligible patients no sooner than 30 days before the scheduled surgery date to minimize the number of ineligible patients after randomization or deviate from the intervention. Participants are retained in the group to which they were originally allocated (“as randomized” analysis). However, patients with missing data on primary outcomes will be excluded from the study. The patient exclusion will be recorded and made explicit in the results.

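### Eligibility is worded as a segmentectomy already performed but must be met at randomization, before surgery; read literally, it could remove randomized patients for a reason the planning method may influence

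*Protocol article*

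**What the plan says.** Four parts of the protocol article bear on who is in the trial.

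- **Eligibility criteria.** The list opens with "Patients eligible for the trial must comply with all the following at randomization". Its first item is "Segmentectomy performed through a MI approach (VATS or RATS", which describes a completed operation. The histology item, confirmed on the removed tissue, and the open-approach exclusion are also worded as facts known after surgery.
- **Participant timeline.** The people approached are those for whom the operation is planned: "Patients selected for MI segmentectomy will conduct an informational interview and possibly sign the consent to the study". Those who agree are then randomized, and operative data are collected later.
- **Data collection.** Centers are encouraged to enroll and randomize "no sooner than 30 days before the scheduled surgery date to minimize the number of ineligible patients after randomization or deviate from the intervention". So randomization precedes surgery, and some ineligibility after randomization is expected. The same section says "Participants are retained in the group to which they were originally allocated" and names one exclusion: "patients with missing data on primary outcomes will be excluded from the study".
- **Primary objective.** The question is whether adding 3D reconstruction "improves the oncological radicality of sublobar resections and prevents major intraoperative complications".

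The article does not say what happens to a randomized patient whose resection turns out not to be a segmentectomy.

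**The concern.** The article gives two definitions of the trial population. One is patients planned for segmentectomy, and the other is patients in whom it was done. They differ by exactly those patients whose resection changed between randomization and the end of surgery.

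That would matter little if the change had nothing to do with the arm. Here the randomized intervention is a planning method, and the Research hypothesis is that it plans segmentectomy better. It is plausible, though not stated, that planning affects which resection is finally done. A 3D reconstruction might lead the team to revise the plan before surgery. Anatomy misjudged on 2D images might lead to a larger resection during surgery. Surgeons know the arm (Blinding), so the decision that settles eligibility would be made with that knowledge.

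If such patients were set aside as ineligible, the groups compared would no longer be the groups randomized, and both the margin and the conversion comparison could be distorted. The issue arises even when surgery stays minimally invasive, so correcting the open-approach exclusion alone would not remove it.

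**Working it through.** **Step 1. Order of events.**

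| Event | Section | Timing |
|---|---|---|
| Selected for minimally invasive segmentectomy | Participant timeline | before randomization |
| Criteria must be met | Eligibility criteria | at randomization |
| 2D or 2D + 3D planning by arm | Interventions | after randomization, before surgery |
| Segmentectomy performed | Eligibility criteria, first item | at surgery |

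The first item cannot be known at the time it must be met. It becomes known only after the randomized planning has been used.

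**Step 2. Does the as-randomized sentence settle it?** It fixes the arm in which a participant is counted. It does not say that someone who fails a criterion discovered at surgery is still counted. The one named exclusion, missing primary outcome data, would not by itself remove a minimally invasive lobectomy, which can have a margin and a conversion status. The text therefore neither requires nor rules out removal.

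**Step 3. The plan's own figure.** Inputs from Sample size: conversion 9.4% (2D) and 2.6% (3D), one-sided 5%, 80% power, 274 required, 288 planned. With the arcsine formula used by the R package that the plan names:

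- h = 2·asin(√0.094) − 2·asin(√0.026)
- n per arm = 2·((z₀.₉₅ + z₀.₈₀)/h)² = 138.01

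The total is 276 (278 after rounding each arm up), close to the stated 274. The planned difference is 9.4 − 2.6 = 6.8 points.

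**Step 4. Possible bias.** The article gives no rate of changed resection, so the inputs here are assumptions. Let the true conversion rate be 9.4% in both arms (no effect), L the share of an arm dropped, and c the conversion risk among those dropped. Then

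retained rate = (0.094 − c·L)/(1 − L)

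with L = 10% in 2D and 5% in 3D:

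| c | 2D retained | 3D retained | Spurious difference |
|---|---|---|---|
| 9.4% (average) | 9.4% | 9.4% | 0 |
| 30% | (0.094 − 0.030)/0.90 = 7.1% | (0.094 − 0.015)/0.95 = 8.3% | 1.2 points against 3D |
| 50% | (0.094 − 0.050)/0.90 = 4.9% | (0.094 − 0.025)/0.95 = 7.3% | 2.4 points against 3D |

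Swapping the two loss shares gives the same differences in favor of 3D. Equal losses of 5% with c = 30% give 8.3% in both arms and no difference. In this no-effect setting, bias needs losses that differ by arm and that carry a conversion risk different from average.

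**Step 5. Power.** The allowance is 288 − 274 = 14 patients (14/288 = 4.9%), and it is for loss at follow-up. On the same arcsine basis, power is 81.5% at 288, 79.7% if 5% are dropped and 77.8% if 10% are dropped. This is the smaller part of the problem.

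**The case against.** The strongest reply is that the wording is loose but the intent is clear. Criteria that must be met before surgery can only sensibly refer to the planned operation, and Participant timeline says as much. Conversion to thoracotomy is a primary outcome, which would make no sense if the minimally invasive criterion were applied to the finished operation. Allocation randomizes those who meet the criteria, and Data collection then keeps them in their group. Ineligibility after randomization might mean benign histology, not a changed resection. Detailed handling may also sit in a full protocol or analysis plan that is not shown.

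Much of this stands. Three stronger readings are tempting and should not be drawn:

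- A reader might infer that patients who receive a lobectomy will be removed. No section says so; it follows only from applying the criterion literally.
- A reader might infer that 3D planning is known to change the type of resection. The article describes it as giving better knowledge of the anatomy and reports no rate of change. The link to arm is an inference from the trial's hypothesis.
- A reader might set an assumed number of changed resections beside the roughly 144 × 0.026 = 3.7 conversions expected in the 3D arm and conclude that the result could easily turn. That comparison does not measure bias, which depends on how losses differ by arm and on the risk of those lost.

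The reply does not remove the contradiction. If planned segmentectomy was meant, the criterion is stated wrongly. If performed segmentectomy was meant, the comparison is not the randomized one. Eligibility is the protocol's own content, so its wording cannot be assumed to be put right elsewhere.

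**Conclusion.** The point holds as a contradiction in the eligibility wording that leaves room for selection after randomization. It is not a demonstrated bias. Whether anyone would be dropped depends on how sites and analysts read the criterion. Whether that would matter depends on a change-of-resection rate, a difference between arms and an excess risk, none of which the article gives. Under the assumptions shown, the distortion is modest beside the planned 6.8-point difference, and its direction cannot be known in advance. It still deserves correction, because the selection would act on the randomized comparison itself and the correction is simple.

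**What to change.** Reconcile Eligibility criteria, Participant timeline and Data collection as follows:

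1. Define inclusion as minimally invasive segmentectomy planned by the multidisciplinary board, with the plan recorded before randomization and before any 3D reconstruction is made.
2. State that every randomized patient who is operated on stays in the primary as-randomized analysis, whatever resection is done.
3. Record planned and performed resection for each patient and report both by arm.
4. Use patients with a performed segmentectomy only as a sensitivity set.

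This does not require redefining the margin endpoint, whose definition is in a supplementary file not shown here.

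The cost is a wording amendment and one additional REDCap field. The downside is that a few resections other than segmentectomy enter the primary analysis and may slightly dilute the effect.
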